## Abstract

**Background:**

Although endovascular mechanical thrombectomy demonstrates clinical efficacy in posterior circulation acute ischemic stroke (AIS), only one third of these patients attain functional independence with a third of patients’ expiring despite vascular recanalization. Neuroprotection strategies, such as therapeutic hypothermia (TH) have been considered a promising adjunctive treatment in AIS. We propose the following rationale, design and protocol for a prospective randomized controlled trial (RCT) aimed to determine whether Vertebrobasilar Artery Cooling Infusion (VACI) improves functional outcomes in posterior circulation AIS patients post mechanical thrombectomy.

**Methods:**

Subjects in the study will be assigned randomly to either the cooling infusion or the control group in a 1:1 ratio (*n* = 40). Patients allocated to the cooling infusion group will receive 300 ml cool saline at 4C through the catheter (30 ml/min) into vertebral artery after thrombectomy. The control group will receive the same volume of 37C saline. All patients enrolled will receive standard care according to current guidelines for stroke management. The primary outcome is symptomatic intracranial hemorrhage (ICH), whereas the secondary outcomes include functional outcome score, infarction volume, mortality, ICH, fatal ICH, cerebral vasospasm, coagulation abnormality, pneumonia and urinary infection.

**Discussions:**

This study will determine the preliminary safety, feasibility, and neuroprotective benefits of VACI in posterior circulation AIS patients with reperfusion therapy. The results of this study may provide evidence for VACI as a new therapy in posterior circulation AIS.

**Clinical Trial Registration::**

www.chictr.org.cn, ChiCTR2200065806, registered on November 15, 2022.

## Introduction

Although mechanical thrombectomy (MT) has improved functional outcomes of patients with acute ischemic stroke (AIS) from anterior circulation large vessel occlusion (LVO), data remain less definitive for posterior circulation LVO (Goyal et al., 2016). BEST and BASICS randomized controlled trials (RCTs) did not show significant efficacy of MT in AIS patients with basilar artery occlusion. Conversely, the recent BAOCHE and ATTENTION study provided high-level evidence-based data on the efficacy of posterior circulation thrombectomy, suggesting some effectiveness of MT for patients with basilar artery occlusion (Jovin et al., 2022; Tao et al., 2022). However, similar to anterior circulation thrombectomy, there remains an apparent discrepancy between the successful recanalization (about 90%) and the ability to achieve functional independence after stroke. Only 46% of patients achieved good functional prognosis (mRS 3) at 90 days with more than a 30% mortality rate (Jovin et al., 2022; Tao et al., 2022). We feel more attention must be given to post reperfusion neuroprotection to improve outcomes. The development of rapid and effective neuroprotective strategies is necessary to supplement endovascular reperfusion. Currently no ideal neuroprotection options exist. In this study, we therefore hypothesized Vertebrobasilar Artery Cooling Infusion (VACI) may benefit AIS patients with posterior circulation LVO after endovascular recanalization.

Therapeutic hypothermia (TH) has been shown to be effective in neonates suffering from hypoxic ischemic encephalopathy and patients suffering from cardiac arrest at the clinical level (Edwards et al., 2010; Choi et al., 2012; Nielsen et al., 2013). In recent years, TH has also been considered a promising neuroprotective treatment after AIS and numerous studies have consistently suggested that TH induces multiple synergistic neuroprotective effects in experimental models (Li et al., 2022). Local surface cooling and systemic hypothermia are commonly used in clinical trials. Studies have shown hypothermia in ischemic stroke to be safely inducible (Choi et al., 2012), although few clinical studies have demonstrated efficacy (Wu et al., 2022). Selective endovascular cooling in ischemic brain is a promising approach for neuroprotection. This modality has the potential not only to achieve more rapid cooling but also to avoid the complications related to systemic TH (Wu et al., 2022). A prospective study of 113 consecutive anterior circulation AIS patients suggested that selective intra-arterial cooling infusion targeted into an ischemic brain tissue after endovascular recanalization appears to be safe and can reduce infarct volume (Wu et al., 2018).

Although TH has been performed on anterior circulation AIS patients in vast majority of clinical trials, few studies have assessed TH on posterior circulation stroke. Moreover, to our knowledge, no intra-arterial and selective hypothermia combined with MT for posterior circulation patients has been reported. In the modern mechanical thrombectomy era, reperfusion can be established in most LVO patients and provides an avenue for intra-arterial hypothermia. In order to improve the current outcomes associated with high disability and mortality rates in posterior circulation AIS, therapeutic hypothermia, as a classical neuroprotective strategy, is worth being investigated after recanalization with MT. Thus, we designed this single-center, prospective study to evaluate the safety, feasibility, and preliminary efficacy of intra-arterial regional cooling infusion, the VACI, in posterior circulation AIS after mechanical thrombectomy.

## Methods/design

This study has been approved by the ethics committee of Beijing Luhe Hospital, Capital Medical University, Beijing, China and registered at www.chictr.org.cn (ChiCTR2200065806) in November 2022.

### Study design

This trial is a single-center, prospective, randomized controlled study that aim to evaluate the preliminary safety, feasibility, and efficacy of intra-vertebrobasilar regional hypothermia after MT in posterior circulation AIS patients within 8 h of symptom onset. A physician unaffiliated with the study will monitor the health and safety status of the participants.

### Participants and screening

Eligible participants will be enrolled consecutively after endovascular therapy for acute posterior circulation LVO from stroke center in the Beijing Luhe Hospital, Capital Medical University. Informed consent will be obtained from each participant or an appointed legal representative if the participant lacking decision-making capacity. The flow chart of screening and enrolling see Figure 1.

**Figure 1 fig1:**
[figure not shown]
Flowchart of the study.

The inclusion criteria include: (1) age between 18 and 80 years, (2) clinical diagnosis of AIS, (3) posterior circulation LVO confirmed by CTA, MRA or DSA (defined as V4 segment of vertebral artery, basilar artery and posterior cerebral artery), (4) <8 h from onset of symptom to femoral artery puncture, (5) baseline NIHSS (National Institute of Health stroke scale) score ≥8.

The exclusion criteria include: (1) pre-stroke modified Rankin Scale (mRS) >2, (2) evidence suggesting spontaneous vessel recanalization, (3) no vessel recanalization (TICI score ≤1) achieved, (4) rapid neurological recovery after vessel recanalization (NIHSS <6), (5) brain images that indicate large area of bilateral cerebellar ischemia or an bilateral extended brainstem ischemia, (6) severe arterial blood pressure >185/110 mmHg, (7) laboratory studies with evidence of coagulation disorders, (8) blood glucose <2.7 or >22.2 mmol/l, (9) severe cardiac dysfunction, (10) pregnancy, (11) no informed consent able to be obtained, (12) enrolled in other clinical studies within 3 months.

### Randomization and blindness

The eligible patients will be enrolled and randomly allocated to the two groups in a 1:1 ratio (*n* = 40) using a computer-generated randomization method. With the use of opaque envelops, all researchers including interventionalists, outcome assessors, and investigators responsible for data collection and analysis will be blinded to the study.

### Interventions

All endovascular procedures were performed under local anesthesia with/without sedative agents. The eligible patients will be randomly allocated to the cooling infusion or control group. All patients within the two groups will receive standard care according to current guidelines, including antiplatelet or anticoagulation treatment, hyperglycemia and hyperlipidemia management, antihypertensive drugs, and treatment of complication. In cooling infusion group, 300 ml 4C cool saline (30 ml/min) will be given in the vertebral artery through a catheter after vessel recanalization as soon as possible (Figure 2). The control group will receive 300 ml 37C saline (30 ml/min) infused into vertebral artery through a catheter. An in-vitro study has demonstrated, 4C cold saline infused at a rate of 30 ml/min through a microcatheters (Excelsior XT-27, Stryker, 2.7F) submerged in a constant temperature bath at 37C (simulating human blood temperature) resulted in the 4C saline that exited from the catheter tip being at 22.1 ± 1.1C (*n* = 6). This would represent the temperature the patient would experience intracranially.

**Figure 2 fig2:**
[figure not shown]
Sketch map of the VACI procedure.

### Outcomes and assessment procedures

The demographic information, risk factors for stroke, comorbidities, occlusion site, procedure of MT, blood pressure, heart rate, finger oxygen saturation, rectal temperature, biochemical indexes before, during, and after VACI will be recorded. NIHSS scores at admission will be determined and collected for further analysis. NIHSS and mRS score will also be evaluated at 24 h, 7 and 90 days after stroke onset. The mRS is a graded interval scale (range, 0 point indicating no symptoms to 6 point indicating death) for the evaluation of neurological functional disability (Hong and Saver, 2009), which will be assessed by trained neurologist blinded to the study. Computerized tomography (CT) will be performed at 24 h after mechanical thrombectomy or whenever any sign of neurological deterioration. Magnetic resonance imaging (MRI) will be performed in a week to evaluate infarction area. Infarct volume will be measured on a Siemens Syngo. *Via* workstation with diffusion-weighted MRI according the method in our previous study (Cheng et al., 2021). Degree of vascular recanalization will be assessed by the modified Thrombolysis in Cerebral Infarction (mTICI) scale (Tung et al., 2017), which will be evaluated by 2 neuroradiologists who are blinded to the assignment of treatment-group.

#### Primary outcomes

The primary outcome of the trial is the incidence of symptomatic intracranial hemorrhage (ICH). ICH is classified into 5 categories according to the European Cooperative Acute Stroke Study II (ECASS 2) (Hacke et al., 1998). Symptomatic ICH (sICH) was defined as parenchymal hemorrhage type I or II diagnosed according to ECASS 2 with an increase in the NIHSS score more than 4-point.

#### Secondary efficacy outcomes

*We will determine*: (1) mRS score at 90 days, (2) favorable prognosis at 90 days (as determined by mRS scores of 0 to 3), (3) mRS scores of 0 to 2 at 90 days, (4) NIHSS scores at 24 h, 7 days, and 90 days, and (5) final infarct volumes.

*Secondary safety outcomes*: Include (1) mortality (mRS score 6), (2) ICH and fatal ICH, and (3) cerebral vasospasm, coagulation abnormality, pneumonia and urinary infection.

### Estimation of sample size

VACI techniques will be the first attempt to our knowledge to address the effect of intra-arterial regional cooling in the posterior circulation. This study will examine the study design, methods, procedures, inclusion criteria, and operational strategies. The results will be used to estimate the sample size and conduct a power analysis for a phase-2 trial. According to previous study in determining sample size for pilot studies (Hertzog, 2008), 10–20 participants enrolled in each group may be sufficient to assess the preliminary trend of safety and feasibility of intra-arterial regional cooling infusion. Therefore, a similar number of 40 participants will be enrolled in this pilot study.

### Statistical analyses

In this study, the intention-to-treat (ITT) principle will be applied to examine end-point events. If the results suggest no difference in the incidence of adverse events found between two study groups and a potential trend of improving functional outcome in cooling infusion group are seen, we will move forward with a phase-2 trial. Before any statistical analysis, the Kolmogorov–Smirnov normality test and equal variance test will be first performed. For normally distributed continuous variables, a two-sided *t*-test will be performed on independent samples to detect the differences between two groups. For continuous variables lacking a normal distribution, a Mann–Whitney U test will be applied. Chi-square or Fisher exact tests will be performed when appropriate for categorical variables. *p* < 0.05 will be considered statistically significant. Statistical analysis will be performed on SPSS 22.0.

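### A normality pre-test at 20 per arm chooses the test for the continuous secondary outcomes, and calling the mRS an interval scale leaves a comparison of mean mRS open

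*Protocol article*

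**What the plan says.** The Statistical analyses section places two checks ahead of every comparison: "the Kolmogorov–Smirnov normality test and equal variance test will be first performed". Continuous variables judged normal go to a two-sided t-test. For the rest, "For continuous variables lacking a normal distribution, a Mann–Whitney U test will be applied". Categorical variables follow a separate rule that does not depend on the pre-test: "Chi-square or Fisher exact tests will be performed when appropriate for categorical variables".

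The section Outcomes and assessment procedures states: "The mRS is a graded interval scale", running from 0 to 6 with 6 meaning death. The secondary efficacy outcomes list the 90-day mRS score as an item of its own, apart from the 0–3 and 0–2 dichotomies, and also list NIHSS at three times and final infarct volume. The article assigns none of these to a specific test and names no ordinal method.

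On size, the plan is that "a similar number of 40 participants will be enrolled in this pilot study", allocated 1:1.

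**The concern.** Two statements combine badly.

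First, the comparison is chosen from the trial data by a test with little ability to detect non-normality in 20 patients. Non-rejection is then read as normality.

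Second, the mRS is an ordinal scale. Labelling it interval points the mRS score toward the continuous route and its normality gate. If the gate opens, the arms are compared on mean mRS, which treats every step as equal, including the step from 5 to death.

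The two branches answer different questions: a difference in means, or a tendency of one arm to rank better than the other. This matters because the pilot has a stated onward use. The Statistical analyses section makes a phase-2 trial depend partly on a possible trend in functional outcome, and Estimation of sample size says the results will feed the phase-2 sample size and power. The quantity carried forward should not depend on a pre-test result.

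**Working it through.** **The plan's own figure.** 40 patients at 1:1 gives 40 / 2 = 20 per arm, the upper end of the pilot rule that "10–20 participants enrolled in each group may be sufficient to assess the preliminary trend of safety and feasibility". This reproduces. The protocol gives no power, effect size or SD, so no sample-size formula applies.

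**What the gate covers.** It governs NIHSS, infarct volume and, if treated as it is labelled, the mRS score. Symptomatic ICH, mRS 0–3, mRS 0–2, mortality and the other safety events are categorical and go to chi-square or Fisher.

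**What equal spacing implies.** In an arm of 20, one patient moving from mRS 5 to death raises the mean by 1/20 = 0.05. One patient moving from 1 to 0 lowers it by 0.05. The mean is unchanged, so the extra death is cancelled.

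**Inputs for the simulation.** The Introduction gives 46% with a good outcome (mRS 0–3) and mortality above 30%. The Discussion gives about one third independent. Assumed bands:
- mRS 0–2: 33%
- mRS 3: 46 − 33 = 13%
- mRS 6: 30%
- mRS 4–5: 100 − 46 − 30 = 24%

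The splits within these bands are assumed. So are the log-normal shape for infarct volume, the effect sizes and the Kolmogorov–Smirnov version. Split E is a variant with 46% at 0–3 and 32% deaths. Runs used 20 per arm and generally 4,000 trials or more (3,000 for the log-normal pass rates by sigma).

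**How often both arms pass as normal (p ≥ 0.05 in each)**

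| Assumed distribution | K–S uncorrected | Lilliefors |
|---|---|---|
| mRS A: .08/.13/.12/.13/.14/.10/.30 | 95% | 18% |
| mRS B: .03/.10/.20/.13/.12/.12/.30 | 94% | 9% |
| mRS C: .11/.11/.11/.13/.16/.08/.30 | 95% | 19% |
| mRS D: .05/.13/.15/.13/.07/.17/.30 | 91% | 5% |
| mRS E: .06/.12/.14/.14/.14/.08/.32 | 89% | 13% |
| Log-normal, sigma 0.5 | 98% | 42% |
| Log-normal, sigma 0.8 | 86% | 12% |
| Log-normal, sigma 1.0 | 63–69% (separate runs) | 4–5% |

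Testing the pooled 40 instead, mRS splits A to D pass in 53–79% (uncorrected) and 0.5–5% (Lilliefors). The t-test route is therefore usual or uncommon depending on the version of the test and on whether arms are tested separately.

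**Consequences for error rates.** The gated rule uses the t-test if both arms pass, otherwise Mann–Whitney.

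| Scenario | Mann–Whitney throughout | Gated, uncorrected | Gated, Lilliefors |
|---|---|---|---|
| mRS A, no effect | 4.3% | 4.8% | 4.3% |
| mRS A, common OR 2 | 21.7% | 22.7% | 21.9% |
| mRS A, common OR 3 | 47.9% | 49.7% | 48.3% |
| Volume, sigma 1, log shift 0.8 | 67.2% | 63.4% | 67.3% |

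For the mRS the two tests disagree on significance in about 1% of null trials and 3–4% at OR 2 to 3. For skewed volumes the gated rule loses 67.2 − 63.4 = 3.8 points with uncorrected K–S and nothing with Lilliefors (67.2 − 67.3 = −0.1). NIHSS was not simulated.

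**The case against.** The strongest reply is that little of consequence rests on this. The affected outcomes are secondary, the trial is a pilot, Study limitations ranks efficacy second, and the progression rule asks for a trend rather than a significant p-value. Matching tests to endpoints is also work that a condensed article may leave to a fuller document.

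Much of this stands and limits the point. It does not remove it. The article did not leave the method open: it states a data-dependent selector and gives the mRS a wrong scale type. A progression rule based on a trend still needs to know whether the trend is in means or in ranks.

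Several stronger readings are tempting and are not supported:
- *That every outcome passes through the gate.* The rule is confined to continuous variables, so the primary outcome is untouched.
- *That the protocol plans a t-test on the mRS.* It does not say so. That route follows only from reading two sections together, and Mann–Whitney or a categorical test is equally open.
- *That power for infarct volume falls by about 16 points.* That gap (51.1% against 67.2%) is for a t-test used always, which is not the plan. The gate diverts many of the samples in which the t-test does badly.
- *That the missing fallback after a failed equal-variance test is an error.* It is detail that a fuller document may supply.

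**Conclusion.** The point holds for the continuous secondary outcomes and is modest in size. The interval label is wrong on the face of the document, and the pre-test is a poor selector at 20 per arm. Under the assumed distributions the share of trials sent to the t-test runs from about 90% down to 5–19% for the mRS, and from about two thirds down to 4–5% for log-normal volumes with sigma 1, on the test version alone.

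A reader might infer inflated false positives or a material loss of power. Neither appears: type I error is near 5%, mRS power is the same to within about 2 points, and the loss for skewed volumes is about 4 points or none. The real cost is interpretation, because the functional effect taken into phase-2 planning may be a mean difference or a rank comparison according to the data.

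The pass rates and power figures rest on assumed distributions and effect sizes. The scale label and the selection rule rest on the text alone.

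**What to change.** - In Outcomes and assessment procedures, describe the mRS as ordinal.
- In Statistical analyses, remove the normality test as the selector of method.
- State in advance one analysis for the 90-day mRS score, either Mann–Whitney or proportional odds, and Mann–Whitney for NIHSS and infarct volume. No t-test is then used for these outcomes, so the equal-variance test has no role for them.
- Leave the chi-square and Fisher rule for categorical outcomes as it is.

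The cost is wording only, and N stays 40. The downside is a trivial loss of power if one of these variables is in fact normal.

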### Study limitations

This proposed study has several limitations. First, it is a single-center trial with a small sample size, which may influence the generalizability of the conclusions and may potentially invite confounding results to the study. Second, the target volume and velocity of infusion solution needs to be optimized.

The trial is designed to identify the safety, feasibility, and, secondarily, the possible efficacy of VACI combined with MT in posterior circulation AIS patients. The preliminary results will provide the parameters for future clinical trials, purely focusing on efficacy.

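### Secondary efficacy outcomes are compared only by unadjusted two-sample tests, although admission NIHSS is collected and age is available; at 20 per arm this gives up precision and leaves chance imbalance uncorrected

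*Protocol article*

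**What the plan says.** The Statistical analyses section of the protocol article assigns a test to each type of variable. "For normally distributed continuous variables, a two-sided" t-test "will be performed on independent samples to detect the differences between two groups". Continuous variables that are not normal get a Mann–Whitney U test, and categorical variables a chi-square or Fisher exact test. The threshold is p "< 0.05 will be considered statistically significant". No regression model, ANCOVA or other adjusted comparison is named.

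Under Outcomes and assessment procedures, "NIHSS scores at admission will be determined and collected for further analysis", and demographic information is recorded. Age is also an entry criterion (18 to 80 years). Baseline NIHSS must be at least 8, with no upper limit. The statistical section gives neither variable a role.

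On allocation, Randomization and blindness says: "The eligible patients will be enrolled and randomly allocated to the two groups in a 1:1 ratio". It mentions no stratification. On size, Estimation of sample size says: "Therefore, a similar number of 40 participants will be enrolled in this pilot study".

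The outcomes affected are secondary: NIHSS at 24 h, 7 days and 90 days, mRS at 90 days, and final infarct volume. The primary outcome is symptomatic ICH. Going on to phase 2 depends partly on an apparent functional benefit in the cooled arm, and the results are to be used to size that trial.

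**The concern.** Follow-up NIHSS is measured on the same scale as the admission value, which is the textbook case for adjusting for baseline. With entry open to any NIHSS of 8 or more and to ages 18 to 80, patients may differ widely in prognosis when randomised. With so few patients and no stratification described, the arms can differ appreciably by chance, and an unadjusted comparison carries that difference into the estimated effect.

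This matters because the phase-2 decision looks for a trend, with no numerical threshold. Such a judgement rests on the point estimate, which is the quantity that chance imbalance moves. A functional trend could be created or hidden by a severity difference present before infusion.

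**Working it through.** **Inputs from the article.** There are 40 patients in total, allocated 1:1, so 40/2 = 20 per arm. This is the top of the range the article cites: "10–20 participants enrolled in each group may be sufficient to assess the preliminary trend of safety and feasibility". Alpha is 0.05, stated as two-sided for the t-test. The article gives no power, effect size or SD, so 2 × 20 = 40 is the only figure to reproduce, and it agrees.

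**Assumed input.** The correlation r between the baseline covariates and the outcome is not in the documents. The range used is 0.3 to 0.7.

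**Step 1: chance imbalance.** The standard error of a baseline mean difference is √(2/20) = 0.316 SD.
- P(difference above 0.5 SD in either direction) = 2 × [1 − Φ(0.5/0.316)] = 0.114, about 11%.
- P(difference above 0.3 SD in either direction) = 2 × [1 − Φ(0.3/0.316)] = 0.343, about 34%.

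**Step 2: gain from adjustment, before its cost.** ANCOVA multiplies the residual variance by 1 − r², so 20 adjusted patients per arm are worth 20/(1 − r²) unadjusted ones.

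**Step 3: cost of estimating two covariates.** The expected variance inflation with N = 40 and two covariates is 1 + 2/(40 − 2 − 3) = 1 + 2/35 = 1.057, about 6%. The net equivalent is 20/[(1 − r²) × 1.057] per arm. The difference detectable at 80% power is (1.960 + 0.842) × √(2/n), with n the equivalent number per arm.

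| r | 1 − r² | Equivalent n per arm, before cost | Net equivalent n per arm | Detectable difference (SD) |
|---|---|---|---|---|
| unadjusted | 1 | 20 | 20 | 0.89 |
| 0.3 | 0.91 | 22.0 | 20.8 | 0.87 |
| 0.5 | 0.75 | 26.7 | 25.2 | 0.79 |
| 0.7 | 0.51 | 39.2 | 37.1 | 0.65 |

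A simulation with two covariates, the second adding nothing to the first (20,000 runs), gave 20.7, 25.4 and 37.4 per arm, which agrees with the net column. Adjustment breaks even where (1 − r²) × 1.057 = 1, that is at r of about 0.23.

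**Step 4: error rates.** In simulations with one covariate and no treatment effect (20,000 runs per scenario), the unadjusted t-test kept its overall type I error at 5%. In the runs where the baseline difference exceeded 0.5 SD, its rejection rate was about 8%, 14% and 21% for r = 0.3, 0.5 and 0.7. For ANCOVA it was 4–5%.

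These figures are for a linear model with normal outcomes. None was computed for proportional-odds regression of mRS or for rank-based analysis.

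**The case against.** **The tests are valid.** This stands. A reader might infer that omitting covariates inflates the false-positive rate. It does not: the overall rate is 5%, and the excess appears only conditionally, when a sizeable imbalance has occurred. The issue is efficiency and conditional bias.

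**Adjustment may be in the statistical analysis plan, which is not shown.** The phrase about further analysis of admission NIHSS could point that way. But the article does name its tests for every variable type, and none uses a covariate. The comment is on that stated choice, not on missing detail.

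**NIHSS might be analysed as change from admission.** The article does not exclude this. A change score still has no covariate. With equal SDs its variance factor is 2(1 − r), which is 1.4, 1.0 and 0.6 at r = 0.3, 0.5 and 0.7, each larger than 1 − r² in the table. The article describes no admission infarct volume from which a change could be taken.

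**The gain may be small.** This stands in part. The entry floor on NIHSS and the exclusion of rapid recoverers could weaken the correlation, as could a covariate measured before thrombectomy. At r = 0.3 the net gain is under one patient per arm.

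**The limitations section already discloses the problem.** It says the small single-centre design "may potentially invite confounding results to the study". A reader might take this as an admission of baseline imbalance. It is a general caveat that mentions neither imbalance nor covariates, so it neither proves the point nor answers it.

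**Only secondary outcomes of a pilot are involved.** True, and there is no power target to miss. The functional result nevertheless feeds the phase-2 decision. Adjustment would not make that loosely worded rule more definite.

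**Conclusion.** The point holds as a recommended improvement to a valid but inefficient analysis of the secondary efficacy outcomes. The 0.32 SD standard error follows from the sample size alone, and the 11% chance of a difference above 0.5 SD adds only a normal approximation. The gain depends on an assumed correlation: about 21, 25 or 37 equivalent patients per arm at r = 0.3, 0.5 or 0.7, so it runs from negligible to substantial.

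A reader might go further and quote 27 to 39 per arm for all these outcomes. That range takes only r = 0.5 to 0.7, ignores the cost of estimating two covariates, and carries a linear-model figure over to ordinal and rank-based analyses. The documents do not support it. Nor does the point reach symptomatic ICH, which is binary and probably too sparse to adjust with 40 patients. That age is recorded is inferred from the demographic data and the entry criterion.

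**What to change.** Before any outcome data are seen, prespecify adjusted models as the main analysis of these secondary efficacy outcomes:
- NIHSS: ANCOVA, rank-based if deaths are ranked.
- Infarct volume: ANCOVA on the log scale.
- 90-day mRS: proportional-odds regression.

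Adjust each for admission NIHSS and age only, and report the treatment estimate with its 95% confidence interval. Keep the planned unadjusted tests as supportive, and leave the primary symptomatic ICH analysis unadjusted. Fixing the covariates in advance matters, because adjusting only after an imbalance is seen would be data-driven.

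The cost is small but not nil. No new data, visits or patients are needed. Two degrees of freedom are spent, with about 6% variance inflation if neither covariate is prognostic. The proportional-odds assumption can hardly be checked with 40 patients over seven mRS levels (40/7, under six per level on average). The two dichotomised mRS outcomes are not covered by this change.
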